## Abstract

Burnout among healthcare workers is a significant global concern that affects their well-being and professional efficacy. Yoga has shown promise in reducing burnout and improving mental health outcomes. However, due to their hectic schedules, healthcare workers often struggle to find time for self-care. A 20 min yoga module has been developed specifically for them to address this. So, this study aims to assess the efficacy of a specific 20 min yoga module in reducing burnout among healthcare workers. An open-label, two-arm, randomised controlled trial involving healthcare workers aged 20–35 years participating for 4 weeks. Exclusion criteria included recent illness, respiratory ailments, pregnancy, life-threatening medical conditions or physical inability to perform yoga. After randomisation of 108 participants, they will be equally allocated to either the yoga group (20 min yoga) or the control group (20 min medium-paced walking). The primary outcome will be burnout, whereas the secondary outcomes include stress, anxiety, selective attention and happiness. Data collection: at baseline and after 4 weeks of intervention, compliance is monitored via daily attendance records. Descriptive and inferential analyses will employ intention-to-treat and per-protocol analysis using SPSS 26.0. A study with 20 participants found that a 20 min yoga intervention significantly improved emotional exhaustion, depersonalisation, personal accomplishment, happiness and Spielberger’s State-Trait Anxiety/Six-letter cancellation test scores. Cortisol levels showed trends of reduction but were not significant. These results inform the upcoming main trial. Ethical approval is obtained from the Institutional Ethical Committee via letter number AIIMS/IEC/20/762. The trial findings will be shared through peer-reviewed publications and presentations at conferences. Trial registration number: CTRI/2021/01/030568; Clinical Trial Registry of India.

WHAT IS ALREADY KNOWN ON THIS TOPICBurnout, characterised by emotional, physical and mental exhaustion, is a significant concern among healthcare workers, with global rates of around 17.3% and higher rates in regions like India. Yoga, particularly pranayama and meditation, has been shown to reduce stress and burnout among healthcare professionals.WHAT THIS STUDY ADDSThis study assesses the efficacy of a 20 min yoga module specifically designed to reduce burnout among healthcare workers, aiming to provide a practical and accessible intervention that can be integrated into their demanding schedules.HOW THIS STUDY MIGHT AFFECT RESEARCH, PRACTICE OR POLICYThe findings could inform future research on short, targeted yoga interventions for healthcare workers and potentially influence workplace wellness programmes, offering a feasible solution to address burnout in the healthcare sector.

## Introduction

 Burnout, characterised by emotional, physical and mental exhaustion, stems from chronic workplace stress, according to the International Classification of Diseases−11. Its symptoms include feelings of exhaustion, detachment from one’s job and reduced professional efficacy.^1^ Burnout is a significant concern among healthcare workers worldwide, affecting approximately 17.3% globally and even higher rates in specific regions, such as India, where work-related burnout affects 26.9% of individuals, escalating to 52.8% during the pandemic.^2 3^ These professionals, who span various roles from direct patient care to healthcare management, are susceptible to burnout due to the demanding nature of their work.

Recognising the need to address burnout among healthcare workers, studies have explored alternative interventions such as yoga. Yoga, which incorporates physical postures (asana), controlled breathing (pranayama) and meditation (dhyana), has been shown to improve both physical and mental well-being.^4^ Specifically, pranayama techniques enhance the parasympathetic nervous system, potentially reducing mental stress.^5 6^ The combination of pranayama and meditation reduced burnout among healthcare workers, enabling them to cope with stress more effectively.

Studies have shown significant stress and burnout reduction among healthcare professionals through mind-body therapies such as yoga, which includes specific practices such as naadi-shuddhi pranayama, asana and gentle stretching.^7^ Nurses who participated in yoga for 6 months reported notably lower stress levels.^8^ Because healthcare workers may not have enough time for self-care, a specific 20 min yoga module was developed and validated to reduce burnout among healthcare workers.^9^

Building on existing research, this study aims to assess the efficacy of a 4-week, 20 min yoga module in reducing burnout among healthcare workers. By focusing on a concise and accessible yoga intervention, this study seeks to provide insights into the practicality and effectiveness of integrating yoga into the busy schedules of healthcare professionals. This approach offers a feasible solution for mitigating burnout in this essential workforce.

## Methods

### Trial design

This will be an open-label, two-arm, randomised, controlled trial. The trial design is illustrated in figure 1. This trial follows the guidelines outlined in the Consolidated Standards of Reporting Trials statement.^10^
Table 1 presents the schedule of participant enrolment, time points and the variables assessed during each period per the Standard Protocol Items: Recommendations for Interventional Trials guidelines, which define standard protocol items for clinical trials.^11^

**Table 1 T1:** Schedule of enrolment, intervention and assessments as per Standard Protocol Items: Recommendations for International Trials (SPIRIT)

	Study period					
	Enrolment	Allocation	Post-allocation			Close-out
Timepoint**	**−t_1_**	**0**	**t_0_**	**t_1_**	**t_2_**	**t_3_**
Enrolment:						
Eligibility screen	✔					
Informed consent	✔					
Allocation		✔				
Interventions:						
20 min yoga module						
20 min walking						
Assessments:						
Socio-demographic details			✔			
Salivary cortisol, MBI, Happiness			✔			✔
STAI, SLCT				✔	✔	

.MBI, Maslach Burnout Inventory; SLCT, Six Letter Cancellation Test; STAI, State Trait Anxiety Inventory; t_0_, baseline; t_1_, day 1; -t1, enrolment; t_2_, day 28; t_3_, day 29.

**Figure 1 F1:**
[figure not shown]
Trial design. HCWs, healthcare workers.

### Participants

*The inclusion criteria are*: (1) healthcare worker age ranges from 20 to 35 years; (2) willingness to participate in the study for 4 weeks.

*The exclusion criteria* are as follows: (1) recent illness or surgery; (2) respiratory ailments (asthma, severe cough, cold, etc) refraining from breathing practices; (3) pregnant women; (4) any other life-threatening medical illness and (5) physical inability to perform the yoga module, which will not be included in the trial.

### Sample size

A sample size of 108 with 54 subjects in each arm (attrition rate 15%) is calculated based on an assumed effect size of 0.60 and with a type 1 error (α) of 0.05 and power (β) of 0.80, using the G Power software.^12^

### Sampling

All healthcare workers at AIIMS Rishikesh are included in the study frame. Invitations are being sent via email, departmental WhatsApp groups and physical flyers. Participants who expressed their willingness are contacted and recruited per eligibility criteria. They are provided with information about the study, answered their questions and given written details about the study. The principal investigator obtains informed consent before enrolment and baseline assessments. The recruitment process of the pilot study was started on 1 August 2022 and completed on 30 September 2022. The recruitment process for the main trial began on 1 May 2024 and is ongoing.

### Randomisation

After baseline assessments, participants will be randomly assigned in a 1:1 ratio to either the yoga group (20 min yoga) or the control group (20 min medium-paced walking). A random number sequence will be generated using a computer-generated programme in Microsoft Excel. The allocation sequence will be concealed in sequentially numbered, opaque, sealed envelopes. The corresponding author will generate random numbers and allocate sequences in opaque sealed envelopes.

### Treatments

#### Intervention group

The participants will be provided with a validated ‘20 min yoga module’^9^ comprising loosening exercises, scientific breathing techniques and meditative practices for 4 weeks. Brief details of the 20 min yoga module are presented in table 2.

**Table 2 T2:** Components and steps of the 20 min yoga module

Serial number	Practices	Time duration (in min)
1	Loosening exercises	2
2	Breath awareness	1
3	Alternate nostril yoga breathing (round 1)	5
4	Rest	1
5	Alternate nostril yoga breathing (round 2)	5
6	AUM chanting	2
7	Humming bee breathing	3
8	Breath awareness	1
	Total	20

#### Control group

20 min medium-pace walking with 1600–2400 steps in 20 min, in a day for 4 weeks, will be provided as an intervention for reducing burnout among participants of this group. This walking intervention is metabolically matched to ensure comparability with other physical activity interventions, making it a suitable comparator. To check adherence and establish equality, all participants will download the free health app Google Fit.^13^ The Google Fit app will monitor the steps taken and walking duration.

A description of the interventions using the Template for Intervention Description and Replication checklist is provided in table 3.

**Table 3 T3:** Description of interventions using the TIDieR checklist

Brief name	20 min yoga module’^9^ for the yoga group and 20 min medium-pace walking for the control group
Why	The 20 min yoga module helps reduce burnout and stress among healthcare workers by promoting relaxation through simple movements, breathing and mindfulness. It provides a quick break during busy shifts, easing tension, boosting focus and improving overall well-being. Regular practice can support long-term stress relief and better mental health.
What materials and procedures	Participants in the intervention group will attend 20 min offline yoga sessions 5 days a week for 4 weeks at AIIMS Rishikesh’s public health lab. The control group will engage in medium-paced walking for 20 min 5 days a week, aiming for 1600–2400 steps per session. They will use the Google Fit app to track their steps, distance and duration and submit daily screenshots of the data.
Who provided	The researcher, a certified yoga instructor, will take the yoga sessions, while participants in the control group will practice medium-paced walking independently, with monitoring by the researcher.
How	Participants in the intervention group will attend offline yoga sessions, while those in the control group will engage in medium-paced walking at their convenience.
Where	Offline yoga sessions will occur at the Public Health Lab of the Department of Community & Family Medicine, AIIMS Rishikesh. At the same time, medium-paced walking can be done at home or the workplace, depending on the participant’s convenience.
When and how much	Yoga sessions and medium-paced walking will be performed for 20 min 5 days a week over 4 weeks.
Tailoring	The 20 min yoga module will be adapted to each participant’s capabilities. Similarly, participants in the control group can walk 1600–2400 steps at a medium pace, based on their capability.

TIDieR, Template for Intervention Description and Replication.

### Outcomes

The primary outcome of this study is to compare the changes in burnout among healthcare workers after the daily practice of a 20 min yoga module to walking for a similar duration for 4 weeks. Secondary outcomes are changes in stress levels, anxiety, selective attention, and happiness scores among healthcare workers after the same 4-week intervention.

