### Study tools

Demographic profile: participants’ names, age, sex and other socioeconomic indicators will be recorded.Maslach Burnout Inventory (MBI) will be used to measure burnout. MBI is a 22-item survey that covers three areas: emotional exhaustion (EE), depersonalisation (DP) and personal accomplishment (PA) and uses a 7-point scale for responses. An answer can range from ‘never’ to ‘every day’. All three subscales show high internal consistency, with Cronbach’s α coefficients of 0.85, 0.76 and 0.71.^14^Salivary cortisol levels will be measured using the Human Cortisol ELISA Kit (Diagnostic Biochem, Canada). Saliva samples will be collected using the SpeciMAX Saliva Collection Kit at the start, middle and end of duty hours, before (day 0) and after (day 29) intervention. The samples will be centrifuged at 4000 rpm and stored at −20°C before analysis. For extraction, 100 µL of cortisol-HRP conjugate and wash buffer will be added to 50 µL of each sample. The plates will be shaken at room temperature for 45 min, washed and incubated with the TMB substrate for 15–20 min. The reaction will be stopped with the solution, and the absorbance will be measured at 450 nm using a microplate ELISA reader. Cortisol extraction will follow the method described by Kirschbaum *et al*.^15 16^Spielberger’s State-Trait Anxiety (STAI) Inventory will be used to measure state anxiety. STAI is a psychological inventory based on a 4-point Likert scale comprising 40 self-report questions. The STAI measures two types of anxiety—state anxiety, or anxiety about an event, and trait anxiety or anxiety as a personal characteristic. Higher scores are positively correlated with higher levels of anxiety.^17^ A high degree of internal consistency was observed for each of the 40 items, with Cronbach’s alpha value=0.38 to 0.89, while Cronbach’s alpha for the total scores is 0.86.^18^Six-letter cancellation test (SLCT) for the measurement of selective attention. The SLCT consists of a sheet of 22 rows×14 columns of randomly arranged alphabet letters. The top of each sheet names six target letters. Participants will choose two possible strategies to cancel target letters: (1) all six letters at once or (2) selecting a single target letter at a time. It also suggests that, according to their choice, they follow horizontal, vertical or random paths on the test sheet. They will be asked to cancel as many target letters as possible during a test time of 90. Different randomised arrays of letters on the worksheet are used to compensate for memory effects. SLCT test–retest reliability was found (r=0.781, p=0.002).^19^ This test is directly related to attention measurements. This test has been used in earlier studies on the Indian population.^20^,^22^ Therefore, this test was validated in this study.The self-rated scale of happiness will be used to measure happiness. A single self-rating scale will be used to assess happiness based on the question: ‘Do you feel happy in general?’. Following this question, a series of numbers from 0 to 10 will be written horizontally on one line with equal intervals. The research participants will be instructed: (a) imagine their global estimation and general feelings (not their present states), (b) take note that 0 is the minimum, 10 is the maximum score and (c) circle a number that best seems to describe their feelings. The 1-week test–retest reliability of the single-item self-rated happiness scale is 0.86.^23^

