## Results of the pilot study

A pilot study was conducted to evaluate the feasibility of an intervention. The quality of practice was assessed using a 10-point Likert visual analogue scale, with participants achieving an average mean score of 9 out of 10. This high score indicates strong acceptability among participants, demonstrating their comfort and ability to perform the practices included in the yoga module effectively.

A total of 20 participants were recruited for the pilot study, and informed consent was obtained from each participant. The participants, with a mean age of 31.6±5.3 years, were randomly assigned to either the yoga group (20 min yoga session) or the control group (20 min medium-paced walking). The interventions were delivered in offline classes and conducted at least 5 days a week over 4 consecutive weeks. Burnout scores were measured using the MBI, salivary cortisol levels were assessed with the ELISA technique and happiness scores were assessed using a self-rated happiness scale at baseline and after the 4-week intervention. State anxiety and selective attention were assessed using the STAI and SLCT, respectively, before and after the 20 min intervention at both baseline and after the 4 week intervention. Normality was checked with the Shapiro-Wilk test. Paired and independent t-tests were used for normally distributed data, while the Wilcoxon Signed Rank and Mann-Whitney U tests were used for non-normally distributed data.

Seventeen participants (nine from the yoga group and eight from the control group) completed the intervention. Statistical tests revealed a statistically significant improvement in scores in all the domains of burnout in the yoga group compared with baseline, as shown in table 4. Significant changes were found in EE (p=0.009), DP (p=0.028), and PA (p=0.03) in the yoga group. In contrast, no significant changes were observed in the control group across these domains: EE (p=0.31), DP (p=0.28), and PA (p=0.68).

**Table 4 T4:** Pre and postmean scores of MBI, salivary cortisol, happiness scale, STAI and SLCT in healthcare workers after 4 weeks of intervention

			Yoga group	Control group	P value
MBI					
Emotional exhaustion	Day 0	Pre	24.67±7.05	22.75±8.81	0.631*
	Day 29	Post	19.44±7.09	21±9.18	0.705*
		P value	0.009†	0.31†	
Depersonalisation	Day 0	Pre	7±5.72	5.5±2.98	0.481‡
	Day 29	Post	4.33±3.77	4±3.42	0.423‡
		P value	0.028§	0.324§	
Personal accomplishment	Day 0	Pre	26.56±8.08	24.5±12.92	0.705*

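### The primary outcome is burnout on a three-subscale MBI with no named primary score or success rule, so the single-test error rate and power are tied to no particular result

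*Protocol article*

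**What the plan says.** - **Outcomes:** "The primary outcome of this study is to compare the changes in burnout among healthcare workers after the daily practice". No score, subscale or total is named.
- **Study tools:** "Maslach Burnout Inventory (MBI) will be used to measure burnout", and the instrument "covers three areas: emotional exhaustion (EE), depersonalisation (DP) and personal accomplishment (PA"). Reliability is given for each subscale separately. There is no total score, cut-off or lead subscale, and no statement of how the three combine into one conclusion.
- **Sample size:** the target number is stated once, as follows: "A sample size of 108 with 54 subjects in each arm (attrition rate 15%) is calculated based on an assumed effect size of 0.60". Error rate and power are then given, in the words "with a type 1 error (α) of 0.05 and power (β) of 0.80, using the G Power software". The score to which the 0.60 applies is not given.
- **Analysis of outcomes:** independent t-tests between groups and paired t-tests within groups are planned for all outcomes, with no order of priority.
- **Results of the pilot study and Table 4:** the three subscales are tested separately, with a 0.05 threshold in the table footnote and no total. The text reports: "Statistical tests revealed a statistically significant improvement in scores in all the domains of burnout in the yoga group compared with baseline". The closing paragraph of that section then says that the intervention significantly improved burnout and that these results will inform the main trial.

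**The concern.** The sample size supports one test, but the outcome as described produces three results. Nothing says whether burnout counts as reduced when one subscale is significant, when all three are, or when a particular one is. Those rules have different error rates and different power, so the stated 5% and 80% cannot be assigned to the primary conclusion until a rule is fixed.

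The pilot shows how a headline could be drawn. Its statement that burnout improved rests on three within-group tests in the yoga arm (Table 4: EE p=0.009, DP p=0.028, PA p=0.037). None of the between-arm tests at day 29 was significant (EE 0.705, DP 0.423, PA 0.506). If the main trial is reported in the same way, the reader cannot tell what error rate stands behind the claim.

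**Working it through.** **Inputs.** From Sample size: d = 0.60, alpha = 0.05, power = 0.80, 54 per arm, attrition 15%. From Study tools: k = 3 subscales. Assumed, because not stated: two-sided tests, and a common correlation between the subscale test statistics of 0 to 0.9.

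**1. The plan's own figure.** For a two-sided two-sample t-test, the normal approximation gives n = 2(1.960 + 0.842)²/0.60² = 43.6, so 44 per arm; the noncentral t gives 45. With attrition, 45/0.85 = 52.9, so 53 per arm and 106 in total. The stated 108 agrees within 2. A one-sided test would need 36 per arm, or 43 after attrition, which does not match. The figure is therefore sound for one two-sided comparison of one score.

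**2. Power for one named score.** 54 × 0.85 = 45.9, so about 46 analysable per arm. At d = 0.60 and two-sided 0.05, power is 80% with 45 and 81% with 46 per arm.

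**3. Rule A: any one subscale at 0.05 is enough.** Under independence the chance of at least one false positive is 1 − 0.95³ = 0.143. With correlated normal statistics (simulation, one million draws):

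| Assumed correlation | Chance of at least one false positive |
|---|---|
| 0 | 14.3% |
| 0.3 | 13.6% |
| 0.5 | 12.5% |
| 0.7 | 10.9% |
| 0.9 | 8.4% |

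For two-sided tests on jointly normal statistics, independence is the worst case, so 14.3% is a ceiling.

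**4. Rule B: all three must be significant at 0.05.** Error is at most 5%. With d = 0.60 on every subscale and 45 per arm (normal approximation, noncentrality 0.60 × √(45/2) = 2.85), power is about 54% at correlation 0, 63% at 0.5 and 74% at 0.9.

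**5. Rule C: Bonferroni over three subscales.** Alpha = 0.05/3 = 0.0167. Power per subscale is 66% with 45 and 67% with 46 analysable per arm. Restoring 80% per subscale needs 60 analysable per arm; 60/0.85 = 70.6, so 71 per arm and 142 in total. The chance that at least one subscale passes is higher, from 97% at correlation 0 to 77% at 0.9 with 45 per arm, but only if the effect is 0.60 on all three.

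**6. Pilot mean changes, from Table 4 (9 yoga and 8 control completers).**

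| Subscale | Yoga | Control | Difference |
|---|---|---|---|
| EE | 19.44 − 24.67 = −5.23 | 21 − 22.75 = −1.75 | −3.48 |
| DP | 4.33 − 7 = −2.67 | 4 − 5.5 = −1.50 | −1.17 |
| PA | 29.56 − 26.56 = +3.00 | 26 − 24.5 = +1.50 | +1.50 |

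All three differences favour yoga, taking a rise in PA as improvement, as the pilot text does.

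**The case against.** The strongest reply is that the document is a condensed article and that multiplicity rules are commonly left to an SAP, which is not shown. That holds for the details of adjustment, so the absence of a correction is not the point here. It does not cover the identity of the primary score or the score behind the sample size. The article has a section on each and leaves both open, while giving laboratory steps for a secondary measure in detail.

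Three stronger readings are tempting, and the document does not support them:

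- **That the trial's error rate is 14%.** This needs a rule that any one subscale suffices, tested at 0.05, with independent subscales. No such rule is stated. The per-test threshold of 0.05 is inferred from the single alpha in Sample size and from the footnote to the pilot table. The pilot stressed improvement on all domains, which does not point to an any-of-three rule.
- **That 5% error and 80% power contradict each other.** They do not. Both hold for one named score or for the first test in a fixed order. They are unassigned, not incompatible.
- **That the pilot subscales point in opposite directions.** Raw day-29 DP means (4.33 against 4) might suggest so, but the yoga arm started higher (7 against 5.5). The named outcome is change, and mean change favours yoga on all three subscales. With 17 completers, nothing further should be read from it.

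**Conclusion.** The point holds as a gap in the definition of the primary endpoint. As written, the plan gives three candidate primary results and no success rule, and its power calculation belongs to no named score. The sample size arithmetic itself reproduces.

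The consequence depends on the rule eventually used: a false-positive chance of about 8% to 14% if any subscale suffices; error within 5% but power of about 54% to 74% if all three are required; or about 67% power per subscale under Bonferroni with 46 analysable per arm. These ranges rest on two-sided tests, d = 0.60 on each subscale where power is quoted, and correlations that the document does not give. The gap itself depends on none of these assumptions. The additional within-group tests and the two analysis sets (intention-to-treat and per-protocol) are not counted in these figures.

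**What to change.** Before any between-arm outcome data are examined, name one MBI score as the sole primary endpoint, tested between arms at two-sided 0.05, and state in Sample size that the 0.60 and the 80% refer to it. The choice is the sponsor's; between-arm change in EE at day 29 is one example. Make the other two subscales secondary, tested in a fixed order or with Holm.

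If all three are to remain primary, state the success rule and restate the power to match it: about 67% per subscale at the first Holm step, or about 54% to 74% if all three must be significant.

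The cost is one sentence each in Outcomes and Sample size. With one named score, the total stays at 108. Recruitment to the main trial began on 1 May 2024 and the trial is open-label, so the change should be made and dated promptly. The downside is that a result on a non-primary subscale alone can no longer carry the burnout claim.

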### Analysis of outcomes

Intention-to-treat (ITT) and per-protocol analyses will be performed to provide a comprehensive understanding of intervention effects. The proportions and means will be calculated for descriptive analysis. The normality of the data will be checked using the Shapiro-Wilk test. Continuous data will be reported as mean±SD and compared using an independent t-test. Categorical data will be reported as frequencies and compared using the χ^2^ test. An independent t-test will compare pre and postintervention data of all group outcomes. A paired t-test will be used to compare the pre and postdata of all outcomes within the group. Statisticians will be blinded to group assignments for statistical analysis. Statistical calculations will be performed by SPSS V.26.0.

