### Data collection and follow-up

Data will be collected at baseline and after fourth week. The researcher will take yoga classes at the Public Health Lab of the Department of Community and Family Medicine, and compliance will be monitored by recording the daily attendance of participants. If a subject cannot attend at least 4 days a week, he/she will not be included in the analysis.

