	Day 29	Post	29.56±8.68	26±12.2	0.506*
		P value	0.037†	0.683†	
Salivary cortisol					
Concentration (ng/mL)	Day 0	Pre	77.89±17.5	71±20.97	0.477*
	Day 29	Post	63.11±25.07	64.13±26.58	0.937*
		P value	0.078†	0.486†	
Happiness scale					
Scores	Day 0	Pre	7.5±1.04	7.8±0.8	0.579*
	Day 29	Post	8.5±1.04	8±1.2	0.218*
		P value	0.007†	0.197†	
STAI					
Scores	Day 1	Pre	35.89±4.05	34.59±3.14	0.469*
		Post	32.66±3.16	34.76±3.33	0.205*
		P value	0.071†	0.922†	
	Day 28	Pre	38.79±5.23	32.04±7.25	0.049*
		Post	30.9±3.28	29.51±5.92	0.566*
		P value	0.017†	0.154†	
SLCT					
Scores	Day 1	Pre	25.89±6.58	26.54±4.89	0.82*
		Post	31.78±7.55	25.06±2.62	0.031*
		P value	0.021†	0.418†	
	Day 28	Pre	32.78±7.6	28.88±8.51	0.338*
		Post	38.67±9.49	30.38±6.95	0.057*
		P value	0.001†	0.255†	

P < 0.05 considered statistically significant.

* Independent t test.

† Paired t test.

‡ Mann-Whitney U test.

§ Wilcoxon Signed Rank Test.

MBI, Maslach Burnout Inventory; SLCT, Six Letter Cancellation Test; STAI, State Trait Anxiety Inventory.

The yoga group showed a trend towards reduced salivary cortisol levels (14.78±21.96 ng/mL), but this change did not reach statistical significance (p=0.078). The control group experienced a smaller decrease in salivary cortisol levels (6.87±26.43 ng/mL), which also did not reach statistical significance (p=0.48), as shown in table 4. Additionally, the yoga group had a significant (p=0.007) increase in happiness scores. Mean pre–post scores of the happiness scale are shown in table 4.

Significant changes were observed in the yoga group across both STAI and SLCT scores following the intervention. On day 1, while the Yoga group showed a non-significant (p=0.071) decrease in STAI scores, there was a significant (p=0.021) improvement in SLCT scores. On day 28, while the Yoga group showed a significant reduction in STAI scores (p=0.017), there was a substantial improvement in SLCT scores (p=0.001). In contrast, the control group showed no significant changes in either STAI or SLCT scores at any time. The mean scores of STAI and SLCT on day 1 and day 28, immediately before and after the intervention, are shown in table 4.

In conclusion, the 20 min yoga intervention significantly improved burnout scores, particularly in EE, DP and PA. While trends towards reduced salivary cortisol levels were noted in the yoga group, these findings did not reach statistical significance. These results will inform the main trial that follows.

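### The four-week STAI and SLCT outcomes are not tied to one pair of measurements, and in the pilot the sign of the STAI effect depends on the pair chosen

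*Protocol article*

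**What the plan says.** All places are in the protocol article.

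- **Outcomes:** "Secondary outcomes are changes in stress levels, anxiety, selective attention, and happiness scores among healthcare workers after the same 4-week intervention". No pair of time points is named.
- **Trial design, Table 1:** STAI and SLCT are ticked at t1 and t2. MBI, salivary cortisol and happiness are ticked at t0 and t3. The key reads "t_0_, baseline; t_1_, day 1; -t1, enrolment; t_2_, day 28; t_3_, day 29". STAI and SLCT are therefore on days 1 and 28, off the baseline/day-29 schedule of the other measures.
- **Data collection and follow-up:** "Data will be collected at baseline and after fourth week".
- **Analysis of outcomes:** "An independent t-test will compare pre and postintervention data of all group outcomes", with a paired t-test within each group. Neither test says whether pre and post refer to a session or to the programme.
- **Results of the pilot study:** STAI and SLCT were taken "before and after the 20 min intervention at both baseline and after the 4 week intervention". The text adds "The mean scores of STAI and SLCT on day 1 and day 28, immediately before and after the intervention, are shown in table 4".
- **Results of the pilot study, reporting:** Table 4's title describes scores following four weeks of intervention, but each paired STAI and SLCT p-value in it compares before with after on one day. The text then states "On day 28, while the Yoga group showed a significant reduction in STAI scores (p=0.017". The Abstract lists STAI and SLCT among the scores that improved significantly and does not mention that the comparison was within a session.

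**The concern.** The stated question is whether four weeks of practice change anxiety and attention. Four measurements per person allow several contrasts, and these answer different questions. A before/after comparison on day 28 estimates the immediate effect of one session. A comparison of the two pre-session scores estimates what has changed over four weeks, free of that day's session. A comparison of day-1 pre-session with day-28 post-session adds the two together.

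The Analysis wording fits any of these. The one worked application, in the pilot, used the first and described the result as improvement following the intervention. If the main trial repeats this, a within-session result would be read as a four-week result. In an open-label trial with several eligible contrasts, the choice could also be made after the data are seen.

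**Working it through.** **Inputs.** Table 4 of the protocol article, mean±SD, with 9 yoga and 8 control completers. A higher STAI score means more anxiety (Study tools).

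| | Day 1 pre | Day 1 post | Day 28 pre | Day 28 post |
|---|---|---|---|---|
| STAI yoga | 35.89±4.05 | 32.66±3.16 | 38.79±5.23 | 30.90±3.28 |
| STAI control | 34.59±3.14 | 34.76±3.33 | 32.04±7.25 | 29.51±5.92 |
| SLCT yoga | 25.89±6.58 | 31.78±7.55 | 32.78±7.60 | 38.67±9.49 |
| SLCT control | 26.54±4.89 | 25.06±2.62 | 28.88±8.51 | 30.38±6.95 |

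**Step 1: reproduce a printed figure.** For day-28 pre-session STAI, the arms differ by 38.79 - 32.04 = 6.75. Welch's t-test gives p = 0.049, as printed in Table 4. The pooled-variance test gives 0.042. The inputs are therefore read correctly.

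**Step 2: difference in change.** For each contrast, take (yoga later - yoga earlier) - (control later - control earlier).

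STAI (negative favours yoga):
- Within the day-28 session: (30.90 - 38.79) - (29.51 - 32.04) = -7.89 + 2.53 = **-5.36**
- Within the day-1 session: (32.66 - 35.89) - (34.76 - 34.59) = -3.23 - 0.17 = -3.40
- Day-1 pre to day-28 pre: (38.79 - 35.89) - (32.04 - 34.59) = 2.90 + 2.55 = **+5.45**
- Day-1 post to day-28 post: (30.90 - 32.66) - (29.51 - 34.76) = -1.76 + 5.25 = +3.49
- Day-1 pre to day-28 post: (30.90 - 35.89) - (29.51 - 34.59) = -4.99 + 5.08 = **+0.09**

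SLCT (positive favours yoga):
- Within the day-28 session: 5.89 - 1.50 = +4.39
- Within the day-1 session: 5.89 - (-1.48) = +7.37
- Day-1 pre to day-28 pre: 6.89 - 2.34 = +4.55
- Day-1 post to day-28 post: 6.89 - 5.32 = **+1.57**
- Day-1 pre to day-28 post: 12.78 - 3.84 = **+8.94**

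The mixed contrast is the sum of the pre-to-pre contrast and the day-28 session effect: for STAI, 5.45 - 5.36 = 0.09; for SLCT, 4.55 + 4.39 = 8.94. The remaining pairing, day-1 post to day-28 pre, compares unlike conditions and is not a sensible endpoint. It gives +8.85 for STAI and -2.82 for SLCT.

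**Step 3: precision.** Table 4 gives no SD of change for STAI or SLCT, so a within-person correlation r must be assumed. In each arm, var(change) = SD1² + SD2² - 2·r·SD1·SD2. The variances are pooled with weights 8 and 7, and SE = √[pooled variance × (1/9 + 1/8)] on 15 degrees of freedom.

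| STAI contrast | Difference | p at r = 0 | p at r = 0.5 | p at r = 0.7 |
|---|---|---|---|---|
| Day-28 within session | -5.36 | 0.18 | 0.07 | 0.03 |
| Day-1 pre to day-28 pre | +5.45 | 0.14 | 0.06 | 0.03 |
| Day-1 pre to day-28 post | +0.09 | 0.98 | 0.97 | 0.96 |

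Example at r = 0.5, pre to pre. Yoga variance: 4.05² + 5.23² - 4.05×5.23 = 22.57. Control variance: 3.14² + 7.25² - 3.14×7.25 = 39.66. Pooled: (8×22.57 + 7×39.66)/15 = 30.55. SE = √(30.55 × 0.2361) = 2.69. The 95% interval is 5.45 ± 2.131×2.69, about -0.3 to +11.2.

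**The case against.** The strongest reply is that measurement around a session is stated only for the pilot. For the main trial, Table 1 has one tick on day 1 and one on day 28, and the data collection text mentions only baseline and the end of the fourth week. Taking day 1 as pre and day 28 as post is a natural reading that agrees with the Outcomes section. This is also a condensed article, and the exact pair for a secondary endpoint may be set out in a fuller document. The first part stands: the before/after-session pattern in the main trial is an inference. It does not settle the matter. Under the two-measurement reading, the article still does not say whether the day-28 score is taken before or after that day's session. And the article goes beyond silence, because its own pilot reports within-session tests under a four-week title.

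Several stronger readings are tempting, and the documents do not support them:

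- *The four-week outcome is confounded with the session effect.* That holds only for some pairs. The pre-session to pre-session contrast is free of the day-28 session. The outcome is undefined, not necessarily confounded.
- *Both instruments reverse.* Only STAI does. All five SLCT contrasts between comparable or ordinary pairs favour yoga.
- *The pilot shows that yoga worsened anxiety over four weeks.* It has 17 completers, and the p-values depend on an assumed correlation. The printed p=0.049 is one unadjusted comparison at a single time point among many.
- *An adverse result was concealed.* Table 4 prints all four means and that p-value, and the text says the scores were taken around the session.

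**Conclusion.** The point holds in limited form. The four-week STAI and SLCT outcomes are not attached to one contrast, and the pilot applied the pre/post comparison to single sessions and reported the results as improvement. In the pilot, the between-arm STAI difference in change moves from -5.36 to +5.45 depending on the pair. SLCT keeps its direction but varies from +1.57 to +8.94, nearly sixfold. This shows sensitivity to the contrast; it does not establish benefit or harm.

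The conclusion that the main trial could repeat the problem assumes that it keeps the pilot's before/after-session measurement, which the shared day-1/day-28 schedule suggests but the article does not state. The p-value ranges assume within-person correlations from 0 to 0.7. Only secondary outcomes are involved. The primary burnout outcome, measured at baseline and day 29, and the sample size are unaffected.

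**What to change.** - In Outcomes, define the four-week STAI and SLCT endpoints as the day-28 pre-session score, compared between arms by ANCOVA with the day-1 pre-session score as covariate. Naming the pair resolves the ambiguity under any between-arm test; the adjustment is a further recommended step.
- List the before/after-session changes on days 1 and 28 as separate acute session effects.
- In Table 1, and under Data collection and follow-up, state when STAI and SLCT are taken relative to the session.
- In Analysis of outcomes, say what pre and post mean for these two instruments.
- Label the pilot's paired STAI and SLCT p-values as within-session in Table 4, the pilot text and the Abstract.

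The cost is wording and minor analysis work. No extra visits are needed if the pilot's measurement pattern is kept. The anxiety result may look less favourable. The Sampling section describes main-trial recruitment as ongoing, so the change should be made and dated before any outcome data are analysed.
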